### Strategies for trial retention

Participants will be asked to monitor adverse events once a week during face-to-face visits. Moreover, phone calls or text messages will be used to remind participants of their scheduled or missed visits.

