### Study outcomes

Outcomes will be evaluated at baseline and at the end of the study (12^th^ week). Outcome assessors and data analysts will be blinded to the intervention assignments. The primary outcome will be HSR.

A set of secondary clinical outcomes will include: Body composition and physical fitness (anthropometric measurements, anthropometric and visceral adipose tissue measurements, dual-energy X-ray absorptiometry scan, peak VO_2_(peak oxygen uptake), basal metabolic rate)Glycemic control (fasting glucose, insulin plasma levels, insulin resistance);Lipid profiles (total, LDL, and HDL-cholesterol cholesterol and triglyceride levels)Gut microbiota composition and diversity;Plasma LPS concentration;Inflammatory cell signaling in peripheral blood mononuclear cells (PBMC):NF-κB; toll like receptor (TLR) 2 e 4, TIR-domain-containing adapter-inducing interferon-β (TRIF), inhibitory-κB kinase (IKK)i/ε, e myeloid differentiation primary response 88 (MyD88);Plasma LPS and PBMC inflammatory response to LPS;Inflammatory/anti-inflammatory markers:C-reactive protein level, tumor necrosis factor(TNF)-α, interleukin (IL)1β, IL-4, IL-6, IL-10, HSP72, adiponectin and leptin);Flow mediated dilation (FMD).

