### Adherence

Adherence to an exercise program was defined as meeting > 80% of the recommended or prescribed exercise doses. Any participant who demonstrates training protocol adherence of 80%, or attends more than 36 sessions, will be considered adherent. Participants will be classified as non-adherent or partially adherent if their adherence is < 80%.

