### Statistical considerations

To assess the effect of exercise on plasma HSP levels between the groups post-intervention, we assumed 80% power, 5% significance level, and an effect size (Cohen’s F) of 0.4. We estimated a dropout rate of 10%, and the calculated total number of patients was 22 in each group.^
24
^

The randomly assigned participants’ data will be analyzed according to the intention-to-treat principle as the primary choice and the per-protocol principle, with treatment, time, and treatment-time interaction registered as fixed effects. We will qualitatively document the reasons for, and details of, each withdrawal case. The normality of the data will be tested using the Shapiro-Wilk test. Mean and standard deviation will be used to describe parametric continuous variables, with median and interquartile range for non-parametric variables, and absolute and relative frequencies for categorical variables. Analysis of variance (ANOVA) will be used to compare the final outcomes. Treatment effects (group, time, and group interaction) will be estimated using Generalized Estimation Equations (GEE), followed by the Bonferroni post-hoc test (P < 0.05). Multiple linear regression analysis (backward method) will be performed to investigate the impact of routine pharmacotherapy, sex, and age on the primary and secondary outcomes. SPSS Professional software (version 20.0; IBM Corp., Armonk, New York, United States) will be used for all analyses.

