### Data collection and management

A questionnaire will be employed to obtain the sociodemographic and clinical characteristics of the participants, including age, sex, marital status, schooling level, diabetes duration, family history of diabetes, use of antimicrobials in the last 30 days, and self-reported physical activity. T2DM drugs will be recorded at baseline and end of the study period.

Anthropometric measures, including body weight, height, calculated body mass index (kg/m^2^), waist circumference, and hip circumference changes will be recorded at the first and last visits. Weight will be measured using a digitally calibrated balance with a maximum capacity of 150 kg and a precision of 100 g. The height will be determined by a vertical statometer attached to the balance with a capacity of 2 m/0.1 cm (Urano, Canoas, Brazil). Waist and hip circumferences will be measured using an inelastic metric tape (2 m/0.1 cm). The total corporal composition will be evaluated using dual-energy X-ray absorptiometry (DEXA scan, Lunar iDXA, GE Healthcare, Buckinghamshire, United Kingdom).

After this evaluation, individuals will perform a self-limited maximal exercise test on a treadmill to determine peak oxygen uptake (VO_2_ peak) and peak HR, supervised by a team of experienced exercise physiologists. The test will be carried out according to the Bruce protocol.^
25
^ Oxygen uptake (VO_2_) and carbon dioxide production (VCO_2_) were determined using a breath-by-breath computerized gas exchange system and analyzed using a 20-second averaging signal. The basal metabolic rate will be analyzed in a fasting state (Quark CPET, Cosmed, Italy).

At the first and last visits to the laboratory, blood samples will be collected and centrifuged at 1,000 × g for 10 min to separate the plasma, which will be stored for further analysis of biochemical parameters. The total glucose, C-reactive protein, HDL cholesterol, HbA1c, and triglyceride levels will be determined using an automated Cobas C111 system (Roche Diagnostics, Basel, Switzerland). LDL-cholesterol will be calculated by the Fried Ewald equation.^
26
^ Insulin resistance was calculated using the Homeostatic Model Assessment (HOMA-IR) method based on insulin and fasting glucose levels.^
27
^

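### The primary analysis is labelled intention-to-treat, but the ANOVA of final outcomes omits anyone without a week-12 value, and the GEE as described does not reliably repair this

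*Protocol article*

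**What the plan says.** Under Statistical considerations, the protocol article sets the analysis principle: data will be "analyzed according to the intention-to-treat principle as the primary choice and the per-protocol principle". The same section assumes 10% dropout and 22 participants per group, and says of those who leave: "We will qualitatively document the reasons for, and details of, each withdrawal case".

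Two methods are then named for the outcomes. The first is "Analysis of variance (ANOVA) will be used to compare the final outcomes". The second is "Treatment effects (group, time, and group interaction) will be estimated using Generalized Estimation Equations (GEE"), followed by Bonferroni comparisons. The article does not say which of the two is primary, and it gives no working correlation for the GEE.

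Study outcomes fixes the schedule: "Outcomes will be evaluated at baseline and at the end of the study", the end being week 12. Data collection and management agrees: "At the first and last visits to the laboratory, blood samples will be collected". There is therefore one post-baseline value per participant.

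Two other sections bear on follow-up. Strategies for trial retention states that "phone calls or text messages will be used to remind participants of their scheduled or missed visits". Adherence states: "Participants will be classified as non-adherent or partially adherent if their adherence is < 80"%. Neither says whether a person who gives up the sessions is still assessed at week 12.

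**The concern.** Intention-to-treat means that everyone randomised is analysed in the assigned arm. An ANOVA of final values cannot do this for a person who has no final value, and with a single post-baseline visit there is no intermediate measurement to draw on. The plan itself expects such people. A result reported as intention-to-treat would then rest on those who reached week 12.

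At stake is the comparability that randomisation provides. If those lost differ between arms in anything related to the outcome, the remaining groups are no longer alike. The GEE might be thought to cover this, since a participant who is lost still contributes a baseline row. Whether that row helps the week-12 contrast depends on a setting that the article leaves open.

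**Working it through.** **Inputs from the protocol article.** 22 per group, three groups (66), 10% dropout, Cohen's f = 0.4, 80% power, 5% significance, one post-baseline assessment.

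**The plan's own figure.** In a one-way ANOVA with three groups and noncentrality f² × N, power is 0.798 at 21 per group and 0.818 at 22. So 22 is the number needed before dropout. With about 20 per arm at week 12, power is 0.776. That is a separate matter from the present point, but it confirms that the planned test is a comparison of final values among those who have them.

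**How many people are concerned.** 0.10 × 66 = 6.6 participants.

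**What each method does with a missing week-12 value.**
- *ANOVA of final outcomes:* the person is excluded.
- *GEE, working independence:* group, visit and their interaction give one free mean per arm and visit, and each is estimated by the raw average of the available rows. The week-12 means are those of the completers, exactly as in the ANOVA. The interaction only subtracts a baseline difference whose expectation is zero under randomisation, so the expected bias is the same.
- *GEE, exchangeable working correlation:* the baseline rows of those lost do inform the week-12 mean.
- *Likelihood-based model on all rows:* week-12 mean = completer mean − slope × (completer baseline mean − baseline mean of all randomised).

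**Illustration (assumptions, not plan figures).** Outcomes in SD units, no true effect, 22 per arm, baseline to week-12 correlation r, 4 participants lost from one arm (18% of that arm; 4/66 = 6% overall, below the planned 10%).

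Loss of the 4 lowest baseline values: the expected values of the four lowest of 22 standard normal observations are −1.91, −1.46, −1.19 and −0.99, sum about −5.54. The remaining 18 have mean 5.54/18 = 0.308 at baseline and r × 0.308 at week 12. This is 0.15 SD for r = 0.5 and 0.18 SD for r = 0.6.

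Simulated bias, active minus control, r = 0.6, 40,000 runs:

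| Who is lost (4 of 22, active arm) | Final-value comparison | GEE, independence | Likelihood model, all rows |
|---|---|---|---|
| Lowest baseline values | +0.18 | +0.19 | 0.00 |
| Lowest week-12 values | +0.31 | +0.31 | +0.21 |
| Highest week-12 values | −0.31 | −0.31 | −0.21 |

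A smaller simulation (400 runs, r = 0.5, Monte Carlo error about 0.02) that includes the exchangeable GEE gave, for baseline-dependent loss, 0.16 (final values), 0.16 (independence) and 0.02 (exchangeable). Losing the lowest week-12 values from the control arm instead gave −0.33, −0.31 and −0.24. Loss of 10% at random in both arms gave 0.01 to 0.02 throughout, which is within simulation error.

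**Scale.** With 2 rather than 4 lost from the arm by lowest baseline, the bias for r = 0.6 is 0.6 × (1.91 + 1.46)/20 = 0.10 SD. If the same kind of loss occurs in both arms, the biases cancel in the difference. For comparison, the standard error of a difference between 18 and 22 participants is √(1/18 + 1/22) = 0.32 SD.

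**The case against.** The strongest reply is that most of what could be asked for here belongs in documents that are not shown. Handling of missing values, assessment after stopping, the working correlation and sensitivity analyses are commonly left to a full protocol or analysis plan, and their absence from an article is no defect. That stands. The point therefore rests only on what the article does fix: an intention-to-treat label, an expected loss of 10%, one post-baseline visit and a test that needs the final value.

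A second reply is that the article names GEE for the treatment effects, and that GEE is not simply a completer analysis. This is partly right. With an exchangeable working correlation, bias from baseline-dependent loss almost disappears (0.02 against 0.16 SD). But the article does not choose that correlation, and it keeps the ANOVA beside the GEE without ranking them.

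A third reply is that a mixed model does not cure outcome-related loss. That is correct: in the illustration it lowers the bias only from 0.31 to 0.21 SD. This is a reason to collect the week-12 values and add a sensitivity analysis. It is no reason to keep the ANOVA.

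Three stronger readings are tempting, and the article does not support them:
- *That people who stop sessions are not assessed.* Nowhere is this stated. Withdrawal from the study, non-adherence and missed visits are treated separately, and the reminders and the separate per-protocol analysis point, if anything, to continued follow-up.
- *That the bias favours the active arms.* Only those arms have sessions to abandon, but unblinded controls who receive nothing can also leave. No dropout by arm is given, and the sign reverses with who leaves.
- *That the last visit could be an early one for someone who stops.* The Abstract and Study outcomes both place the final measurement at 12 weeks, and no early-termination sample is described.

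**Conclusion.** The point holds in a limited form. For participants without a week-12 value, the ANOVA of final outcomes is a complete-case analysis and does not deliver the intention-to-treat principle that the same section makes primary. The GEE repairs this only under a working correlation that the article does not fix. Under independence it is as biased as the ANOVA when loss depends on baseline.

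The size and direction of any bias in this trial cannot be stated. The illustrative 0.18 SD rests on an assumed correlation of 0.6 and on a selective loss of 4 of 22 in one arm. If loss is completely at random, or alike in both arms, there is no bias in the contrast. The matter is worth correcting because the change costs little and week-12 values not collected at the time cannot be recovered later.

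**What to change.** 1. Make one likelihood-based mixed model the primary analysis, in place of the final-value ANOVA and the GEE: group, visit and group-by-visit as fixed effects, with all available rows from all randomised participants. It can be fitted in the SPSS software already named.
2. State that participants who stop the sessions but do not withdraw consent are invited to the already planned week-12 assessment and analysed in the assigned arm.
3. Add one sensitivity analysis for missing week-12 values, because the mixed model is valid only if they are missing at random.

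The cost is a few sentences of wording, the existing week-12 visit for at most about 6 to 7 people at the planned dropout rate, and a little more analysis work. Estimates may turn out somewhat less favourable than among completers alone.

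### The plan gives the same outcomes both an ANOVA of final values and a GEE group-by-time analysis, does not say which decides the primary outcome, and adjusts for baseline as a covariate in neither

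*Protocol article*

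**What the plan says.** All of the analysis text is in the Statistical considerations section of the protocol article.

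- **First analysis:** "Analysis of variance (ANOVA) will be used to compare the final outcomes". No covariate is named.
- **Second analysis, in the next sentence:** "Treatment effects (group, time, and group interaction) will be estimated using Generalized Estimation Equations (GEE), followed by the Bonferroni post-hoc test", with P < 0.05 in parentheses at the end of that sentence.
- **Analysis set:** data are to be "analyzed according to the intention-to-treat principle as the primary choice", with per-protocol as well, "with treatment, time, and treatment-time interaction registered as fixed effects".
- **Sample size:** "we assumed 80% power, 5% significance level" and a Cohen's f of 0.4 for a comparison of plasma HSP levels between the groups after the intervention. With 10% dropout mentioned, the result is 22 per group.

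The Study outcomes section names HSR as the primary outcome and states: "Outcomes will be evaluated at baseline and at the end of the study". A baseline value is therefore planned for each outcome.

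**The concern.** Two inferential analyses address one question, whether the arms differ in HSR after 12 weeks, and the text gives no order between them. Other statements in the section point in opposite directions. The sample size is for a post-intervention group comparison with no baseline term, which is the ANOVA. The fixed effects attached to the intention-to-treat analysis are those of the GEE. The words about a primary choice select the analysis set, not the test. The Bonferroni step covers comparisons after the GEE, not the choice between GEE and ANOVA.

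Two things are at stake. If the two p-values disagree, the protocol does not say which is the trial's result. And the power the trial really has depends on which test decides, although a third standard analysis of the same data would do at least about as well as either.

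**Working it through.** **Inputs from the protocol article:** three arms, f = 0.4, 5% significance level, 22 per group, 10% dropout, outcomes at baseline and week 12.

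**Assumed:** the correlation r between baseline and week-12 values, which the article does not give. Results are shown for a range. Data are taken as normal with equal variance at both visits and none missing among those analysed.

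**Step 1. Which test was the trial sized for?** For a one-way ANOVA with three groups, the noncentrality is λ = f² × N, with 2 and N − 3 degrees of freedom.

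- 21 per group: λ = 0.16 × 63 = 10.08, power 79.8%.
- 22 per group: λ = 0.16 × 66 = 10.56, power 81.8%.

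So 22 is the smallest group size reaching 80% in an ANOVA of final values, before any allowance for dropout. After 10% dropout, 22 × 0.9 = 19.8, or about 20 completers per group: λ = 0.16 × 60 = 9.6, power 77.6%.

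**Step 2. What the GEE interaction tests.** With two visits and complete data, the group-by-time term is the between-arm difference in mean change. The variance of a change score is 2(1 − r) times that of a final value. Adjusting for baseline as a covariate gives 1 − r² times, at the cost of one degree of freedom. Hence, for N = 60:

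- Final value: λ = 9.6 at every r.
- Change: λ = 9.6 / [2(1 − r)].
- Baseline-adjusted: λ = 9.6 / (1 − r²), with 2 and 56 degrees of freedom.

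| r | λ, change | λ, adjusted | Power, ANOVA of final value | Power, interaction | Power, baseline-adjusted |
|---|---|---|---|---|---|
| 0.3 | 9.6/1.4 = 6.86 | 9.6/0.91 = 10.55 | 0.78 | 0.62 | 0.82 |
| 0.5 | 9.6/1.0 = 9.60 | 9.6/0.75 = 12.80 | 0.78 | 0.78 | 0.89 |
| 0.7 | 9.6/0.6 = 16.00 | 9.6/0.51 = 18.82 | 0.78 | 0.95 | 0.97 |

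Simulation of the same settings (60,000 trials each) agrees to within about one point; for the adjusted analysis it gives 0.81, 0.88 and 0.97. At r = 0 adjustment gains nothing: simulated power is 0.77 against 0.78 for the ANOVA.

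**Step 3. False-positive risk if either test may count.** This used 60,000 null trials per setting. Two independent tests would give 1 − 0.95² = 9.75% as a benchmark. Simulated chance that at least one of the two has p < 0.05, at 22 per group:

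| r | Either, interaction by exact F test | Either, interaction by uncorrected robust Wald test |
|---|---|---|
| 0 | 8.5% | 10.2% |
| 0.3 | 8.8% | 10.7% |
| 0.5 | 9.1% | 10.9% |
| 0.9 | 9.8% | 11.8% |

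At 20 per group the ranges are 8.5% to 9.5% and 10.5% to 11.7%. A single baseline-adjusted test stays at about 5% throughout.

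**The case against.** The strongest reply is that the text leans towards one model. Treatment effects are said to be estimated by GEE, the fixed effects of that model are tied to the intention-to-treat analysis, and the ANOVA can be read as supportive. That reading is reasonable, but it is not stated, and the sample size points the other way.

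It is also fair to say that the power comparison concerns efficiency. In a randomised trial both planned comparisons are valid, r is unknown, and the gain over whichever existing test is better is only about 3 to 11 points. That stands, and it limits the weight of the point.

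A reader might infer four stronger criticisms that the document does not support:

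- **That the plan as a whole wastes the baseline.** It does not: the GEE has baseline as its first time point. What holds is that neither analysis uses it as a covariate. For the ANOVA, this is the natural reading of a comparison of final outcomes with no covariate named.
- **That both tests are declared at P < 0.05.** The threshold is attached only to the sentence on the GEE and its post-hoc test. The other 5% belongs to the sample size.
- **That the ANOVA contradicts intention-to-treat.** The article does not restrict it to completers, and handling of missing values may be set out in a document not shown.
- **That the GEE alone exceeds 5%.** That depends on an uncorrected robust variance with about 20 per arm. The article names no variance estimator, and such detail is commonly left to the analysis plan.

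**Conclusion.** The point holds as a free improvement. The article states two analyses of the same outcomes, names neither as decisive for HSR, and supports each in a different sentence. This is a problem in what is written, not a detail left for later.

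The false-positive risk of about 9% is conditional: it applies only if either result may be taken as success, which the article neither says nor excludes. The figure of about 11% needs the further assumption of an uncorrected robust Wald test. The power differences rest on the assumed r. Over 0.3 to 0.7 the baseline-adjusted comparison is better than both planned tests, and it removes the risk of relying on the interaction when r is low (0.62 at r = 0.3).

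**What to change.** State one primary analysis for HSR: the 12-week value compared between the three groups, adjusted for the baseline value. It can be an ANCOVA, or a mixed model with a common baseline mean, visit, group-by-visit and small-sample degrees of freedom. A plain ANCOVA omits participants without a 12-week value. The mixed model keeps them, although with a single post-baseline visit they inform mainly the baseline mean. Keep Bonferroni for the pairwise contrasts, label the GEE a sensitivity analysis, and drop the ANOVA of final values or make it descriptive.

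The cost is a few sentences, settled before the data are analysed. Both models are standard routines, and the baseline measurement is already planned.

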### Allocation

Participants will be randomly assigned to groups according to a sequence of computer-generated random numbers. This sequence will be obtained in Microsoft Excel (Redmond, Washington, United States) in a 1:1 ratio, with blocks of eight or six participants to complete the total number calculated. A sealed envelope containing the allocation code will be opened at the beginning of the treatment in the presence of the participant according to the order of entry into the study.

Owing to the nature of the interventions, the researcher conducting the exercise sessions and participants will not be blinded. To ensure assessor masking, the participants will be asked to omit their assigned groups and not talk about their interventions during the outcome evaluation sessions. In case of unintentional unblinding for any reason, the researcher will notify the principal researcher.

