### Interventions

Volunteers who met the inclusion criteria will be guided through the study and asked to sign a written informed consent form before enrollment in the trial. The participants will be randomized into the following intervention groups: control, RT or HT. In the control group, participants will not receive any intervention. In the intervention group RT, participants will perform supervised exercises in a gymnasium on three non-consecutive days of the week for a total of 12 weeks. Each session will last approximately 60 min and consist of warm-up, resistance training, and cool-down. All sessions will be conducted by qualified sports and exercise scientists.

The RT program will consist of a combination of upper- and lower-body exercises using gymnasium equipment, free weights, and body weight (functional exercises) as the primary resistance. The 12 weeks RT will be divided into three mesocycles of four weeks each (please see details of sets, repetitions, and intervals in Table 1). The exercises will include leg press, knee extension, leg curl, biceps curl, triceps extension, lat pulldown, shoulder press, bench press, and abdominal crunch exercises. Before the start of the training period, the participants completed a familiarization session to practice the exercises they would perform further during the training program when the exercise load was individually tested. Resistance training was performed using two–three sets per exercise at intensities between 12 and 15 maximum repetitions (the heaviest possible weight to perform 12–15 repetitions), as shown in Table 1. The intensity of the functional exercises was controlled using the OMNI scale,^
21
^ with each session lasting 60 min.

**Table 1 T1:** Resistance training program

Mesocycle	Weeks	Repetitions/load	Number of sets	Interval between sets
**1**	1–4	12/15	2	1 min
**2**	5–8	12/15	3	1 min
**3**	9–12	10/12	3	1 min and 30 s

Participants in the HT group will undertake whole body heat treatment according to previous methods.^
22

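### With 20 to 22 participants per arm, uncorrected robust GEE Wald tests would run at about 0.07 for the treatment-by-time effect; name a small-sample method

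*Protocol article*

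**What the plan says.** All of this stands in the protocol article, mostly under Statistical considerations.

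- **Method.** Treatment effects "will be estimated using Generalized Estimation Equations (GEE", with treatment, time and treatment-by-time as fixed effects. A Bonferroni post-hoc test follows, and the P < 0.05 criterion is attached to that step. A separate sentence plans ANOVA to compare the final outcomes.
- **Size.** "we assumed 80% power, 5% significance level, and an effect size" (Cohen's f) of 0.4 lead to the statement that "the calculated total number of patients was 22 in each group". The assumed dropout rate is 10%.
- **Arms and visits.** Under Interventions: "The participants will be randomized into the following intervention groups: control, RT or HT". Under Study outcomes, measurements are taken at baseline and at week 12 only.
- **Not stated.** The article does not give the GEE test statistic, the covariance estimator, the reference distribution or any small-sample correction. SPSS 20.0 is named for all analyses.

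**The concern.** GEE tests are justified for a large number of independent participants. With few per arm, two things go wrong in the uncorrected robust version. The sandwich variance is too small on average, and the chi-square or normal reference treats that estimated variance as known. Both push towards rejection.

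At stake are the error rate and interval width of the analysis to which the article assigns the treatment effects and the pairwise comparisons. That includes the primary outcome, the heat shock response. The distortion is modest, but for near-normal outcomes it always goes the same way: more false positives and intervals that are too narrow.

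**Working it through.** **The plan's own figure.** One-way ANOVA, three groups, f = 0.4, alpha 0.05; power from the noncentral F with noncentrality f² × N and df (2, N − 3).
- 21 per group: 0.16 × 63 = 10.08, power 0.798.
- 22 per group: 0.16 × 66 = 10.56, power 0.818.

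So 22 per group reproduces, as the number before dropout. The sample size thus matches an F test, not a GEE Wald test. Whether dropout was added is a separate matter. Here it only sets the range: 22 × 0.9 = 19.8, so 20 to 22 per arm analysed.

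**Reduction to change scores.** With two visits and complete data, the GEE interaction test compares mean changes across the three arms. The uncorrected sandwich variance of an arm's mean change is Σ(d − d̄)²/n², where the unbiased version is Σ(d − d̄)²/[n(n − 1)]. The standard error is therefore too small by the factor √((n − 1)/n), which is 0.975 at 20 and 0.977 at 22 per arm.

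**One pairwise comparison, normal changes with equal variance.** The robust z statistic, multiplied by that factor, follows a t distribution with 2n − 2 df.
- Nominal 5%, n = 20: P(|t₃₈| > 1.960 × 0.975 = 1.910) = 0.064, so a nominal 95% interval covers about 93.6%. At n = 22 the error is 0.062.
- Bonferroni level 0.05/3 = 0.0167, critical z 2.394, n = 20: P(|t₃₈| > 2.333) = 0.025. At n = 22 it is 0.024.

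**Interaction test, 2 df, robust variance.** Simulated null trials with normal changes, test against chi-square 5.99 (200,000 trials per size):

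| Per arm | Robust Wald, interaction | Any of three Bonferroni pairs | F test on the same changes |
|---|---|---|---|
| 20 | 0.074 | 0.065 | 0.050 |
| 21 | 0.072 | 0.063 | 0.050 |
| 22 | 0.070 | 0.062 | 0.049 |

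A repeat of 100,000 trials gave 0.074 and 0.073 for the interaction at 20 and 22 per arm, and 0.064 and 0.065 for the Bonferroni pairs. Fitted GEE models (exchangeable, within-person correlation 0.5, 4,000 trials, Monte Carlo standard error about 0.004) gave 0.074 with 20 complete per arm. They gave 0.080 with 22 per arm of whom 2 lack week 12.

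**Interaction test, model-based (pooled) variance, chi-square reference.** For 2 numerator df, P(F > x) = (1 + 2x/ν)^(−ν/2), with ν = 3n − 3.
- Divisor n − 1, n = 20: (1 + 5.991/57)^(−28.5) = 0.058. At n = 22: (1 + 5.991/63)^(−31.5) = 0.057.
- Divisor n: the cutoff shrinks by (n − 1)/n, which gives 0.066 at n = 20 and 0.065 at n = 22.

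The fitted models gave 0.070 with complete data and 0.073 with the missing visits, each with a standard error of about 0.004.

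**Skewed outcomes** (log-normal at both visits, correlation 0.5, robust variance, 20 to 22 per arm).
- Log-SD 1.0: interaction 0.055 to 0.056, Bonferroni familywise about 0.044.
- Log-SD 0.5: interaction 0.068, familywise about 0.059.

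**With a correction.** A bias-reduced GEE variance at 20 per arm gave about 0.05 (1,500 trials). Using n − 1 in the sandwich with an F reference gave 0.056, so a simple correction removes most of the excess but not all of it.

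**The case against.** The strongest reply is that the article never says the tests will be uncorrected robust Wald tests. The estimator and any correction are details that a journal article may leave to an analysis plan, and that plan is not shown. This stands. It rules out an inference that a reader might draw, namely that the plan's nominal 5% is in fact 7%. The article does not support that as a statement of fact, and silence about a correction is not in itself a fault. What remains is that the article does choose a large-sample method, for about 20 participants per arm and two visits, when a finite-sample method on the same data holds close to 5%.

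Three further objections limit the point.
- P < 0.05 is attached to the Bonferroni step, not to the interaction test. The figure for that step is the smaller one, 0.062 to 0.065.
- A reader might infer that every outcome is affected alike. The article itself expects non-normal variables, and with strong skew the inflation nearly vanishes for the interaction, while the Bonferroni familywise error falls below nominal.
- A reader might infer that all treatment comparisons are affected. The planned ANOVA of final outcomes uses an F test that keeps its level with normal data, and the article does not rank it against the GEE. It does not, however, correct the GEE P values and intervals that would be reported beside it.

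**Conclusion.** The point holds in conditional form. With 20 to 22 per arm and near-normal outcomes, an uncorrected robust GEE Wald test of treatment by time has a true level of about 0.07. The Bonferroni comparisons have a familywise error of about 0.062 to 0.065, and nominal 95% pairwise intervals cover a little under 94%. With model-based variance the interaction level is about 0.057 to 0.067.

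Assumptions not in the document are the Wald statistic, no small-sample correction, equal arms, normal changes with equal variance for the main figures, and a within-person correlation of 0.5 in the fitted models. The complete-data results for normal changes do not depend on that correlation. The inflation is modest and easily removed, so this is a recommended change and not a flaw that invalidates the trial. Confidence is medium, because the size depends on choices that the article leaves open.

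**What to change.** Under Statistical considerations, for continuous outcomes, replace the GEE with a linear mixed model with the same fixed effects (treatment, time, treatment by time). Test it by F and t tests with small-sample degrees of freedom such as Satterthwaite, and take the Bonferroni comparisons from that model. With complete data and two visits this amounts to an F test on change scores, which held 5% in the check above.

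Alternatively, keep the GEE but state a bias-corrected sandwich variance (for example Mancl-DeRouen or Kauermann-Carroll) with F and t references. The article fixes SPSS 20.0 for all analyses, so the sponsor should confirm that the chosen correction is available there or name other software. For strongly skewed markers, state the transformation or other handling, since a mixed model leans more on normality than GEE does.

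The cost is one or two sentences and no new data, with slightly wider confidence intervals and slightly larger P values.
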